The sample size was calculated based on the co-primary outcome of 7-day point prevalence abstinence (PPA) at week 6. Referring to recent systematic reviews of acupuncture smoking cessation trials (21, 22), a control group abstinence rate of approximately 15% was assumed, with an odds ratio (OR) of 1.9 for the HMA + NRT group. With a two-sided significance level of *α* = 0.05, 80% power, and a 1:1 allocation ratio, a total of 188 participants is required. Accounting for a 15% dropout rate, the final sample size is set at 220 participants (110 per group) (23). The VAS craving outcome, as the other co-primary endpoint, is also adequately powered based on the same sample size. Multiplicity control. Because two co-primary outcomes are designated, the overall type I error rate is controlled using the Hochberg procedure. Under this approach, each outcome is tested at the full *α* = 0.05 level; the family-wise error rate is preserved because the trial is considered positive only if both co-primary outcomes achieve statistical significance (*p* ≤ 0.05 each). This method offers greater power than Bonferroni correction while maintaining strong control of the family-wise error rate.

To monitor expectancy and attention effects, participants will complete the Credibility/Expectancy Questionnaire (CEQ) at baseline and post-randomization; these scores will be explored in sensitivity analyses (16).

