#### Adherence monitoring and data collection

2.4.3

Participants will attend six in-person visits (baseline and Weeks 2, 4, 6, 10, and 24). Each visit will include:

(1) Compliance assessment: NRT patch verification and diary review (VAS scores and adverse events).(2) Outcome assessments (Table 1):

- CO and VAS: all visits.- PPA: Weeks 6 and 24.- SF-36, PSQI, BDI-II, and BAI: baseline and Weeks 4, 6, 10, and 24.

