#### Co-primary outcomes

2.6.1

(1) Nicotine craving intensity will be assessed using a visual analog scale (VAS), consisting of a 100-mm horizontal line ranging from 0 (no craving) to 100 (maximum craving) (31). Participants will indicate their current level of craving by marking a point on the scale. The change in VAS score from baseline to week 6 serves as one of the co-primary outcomes.(2) Seven-day point prevalence abstinence (PPA) will be assessed at week 6. Self-reported abstinence over the preceding 7 days will be biochemically verified using exhaled carbon monoxide (CO). Participants with discordant self-reported and biochemical results (i.e., self-reported abstinence but CO ≥ 6 ppm) will be classified as non-abstinent (33). PPA at week 6 serves as the second co-primary outcome. PPA at week 24 will be analyzed as a secondary outcome.

VAS craving was selected as a co-primary endpoint due to clinical relevance and feasibility, while biochemically verified PPA provides an objective measure of cessation, together addressing both subjective withdrawal and confirmed abstinence (33).

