#### Secondary outcomes

2.6.2

(1) Exhaled carbon monoxide (CO) as a continuous measure will be assessed at all visits to reflect recent smoking behavior (34).(2) Point prevalence abstinence at week 24 will be assessed as a secondary time point using the same definition as the co-primary PPA outcome (self-report + CO < 6 ppm) (33, 35).(3) Quality of life will be assessed using the validated Chinese version of the Short Form 36 Health Survey (SF-36), which includes eight domains of physical and mental health (36).(4) Sleep quality will be assessed using the Chinese version of the Pittsburgh Sleep Quality Index (PSQI) (37).(5) Depressive symptoms will be assessed using the Beck Depression Inventory-II (BDI-II) (38).(6) Anxiety symptoms will be assessed using the Beck Anxiety Inventory (BAI) (39).

Assessment time points for all outcomes are summarized in Table 1.

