#### Two co-primary outcomes will be analyzed as follows

2.10.1

Multiplicity control for co-primary outcomes. Type I error is controlled at the family-wise level using the Hochberg procedure. The trial will be declared positive only if both co-primary outcomes (VAS craving change and PPA at week 6) achieve statistical significance at *p* ≤ 0.05.

The change in nicotine craving intensity measured by the VAS from baseline to week 6 (one of the two co-primary outcomes) will be analyzed using linear mixed-effects models including fixed effects for group, time, and group × time interaction, with participant-specific random intercepts to account for repeated measurements.

The PPA at week 6 (the second co-primary outcome) will be analyzed using generalized estimating equations (GEE) with a logit link function and an exchangeable correlation structure. Results will be reported as adjusted odds ratios (ORs) with 95% confidence intervals (CIs).

For smoking abstinence outcomes, missing smoking-status data will be treated as non-abstinent in the primary analysis. For sensitivity analysis, a pattern mixture model under missing-not-at-random (MNAR) assumptions will be applied, assuming a relapse rate of 80–90% among participants with missing follow-up data (42).

Secondary continuous outcomes will be analyzed using linear mixed-effects models, including fixed effects for group, time, and group × time interaction, and random intercepts to account for within-subject correlation. Models will be adjusted for baseline values where appropriate. SF-36 total scores and PSQI global scores will be analyzed directly, with similar models applied to BDI-II, BAI, and exhaled carbon monoxide (CO).

To control for type I error due to multiple comparisons across the secondary outcomes (BDI-II, BAI, SF-36, PSQI, CO), a false discovery rate (FDR) procedure will be applied. Adjusted *p*-values will be reported alongside unadjusted estimates, and findings will be interpreted with appropriate caution (43).

Prespecified subgroup analyses will include three-way interaction terms (subgroup × treatment × time) within mixed-effects models to explore potential effect modification by sex (male/female) and age (<40 vs. ≥40 years).

Sensitivity analyses will include a per-protocol (PP) analysis excluding participants with less than 80% adherence, defined as attendance at fewer than 14 of 18 acupuncture sessions or NRT use on fewer than 80% of study days.

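### Week-24 abstinence is a declared secondary outcome, but the FDR rule said to cover the secondary outcomes lists only the other five

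*Protocol article*

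**What the plan says.** The protocol article gives week-24 PPA its status twice. Section 2.6.1 (Co-primary outcomes) says: "PPA at week 24 will be analyzed as a secondary outcome". Section 2.6.2 (Secondary outcomes) has it as item (2) of a numbered list of six: "Point prevalence abstinence at week 24 will be assessed as a secondary time point using the same definition as the co-primary PPA outcome". The other five items are exhaled CO as a continuous measure, SF-36, PSQI, BDI-II and BAI.

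Section 2.10.1 states two multiplicity rules. The co-primary rule is: "The trial will be declared positive only if both co-primary outcomes (VAS craving change and PPA at week 6) achieve statistical significance". The rule for the secondary outcomes is that, "across the secondary outcomes (BDI-II, BAI, SF-36, PSQI, CO), a false discovery rate (FDR) procedure will be applied". Adjusted p-values are to be reported for that second family.

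Section 2.4.3 gives the abstinence schedule as "PPA: Weeks 6 and 24", and treatment lasts 6 weeks. The model for abstinence is also specified for week 6 only: "The PPA at week 6 (the second co-primary outcome) will be analyzed using generalized estimating equations (GEE) with a logit link function".

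**The concern.** The FDR sentence claims to cover the secondary outcomes and then names them. The bracketed list is closed, with nothing to mark it as a set of examples, and it is one short of the list in Section 2.6.2. The missing member is week-24 PPA.

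PPA is measured only at weeks 6 and 24, and week 6 is the end of treatment. Week-24 PPA is therefore the only result on verified abstinence after treatment stops. The Limitations section also values verified PPA as less open to expectancy effects than the subjective scales in this unblinded trial. If its family is not fixed in advance, whether its p-value is adjusted could be decided after the result is known, while the text still claims control across the secondary outcomes.

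**Working it through.** **Step 1. Membership of each family, as stated in the article.**

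| Outcome | Status (2.6.1, 2.6.2) | Co-primary rule (2.10.1) | FDR list (2.10.1) |
|---|---|---|---|
| VAS change to week 6 | co-primary | yes | no |
| PPA, week 6 | co-primary | yes | no |
| CO, continuous | secondary (1) | no | yes |
| PPA, week 24 | secondary (2) | no | **no** |
| SF-36 | secondary (3) | no | yes |
| PSQI | secondary (4) | no | yes |
| BDI-II | secondary (5) | no | yes |
| BAI | secondary (6) | no | yes |

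Week-24 PPA is the only efficacy outcome with no entry in either family. No other section tests it conditionally on the co-primaries or calls it exploratory. CO at week 24 is within the FDR family, but as a continuous measure, which is not the abstinence outcome.

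**Step 2. Size, as an illustration.** The article states no error rate for the secondary outcomes, so there is no figure to reproduce. The following inputs are assumptions: Benjamini–Hochberg (BH) as the FDR method, q = 0.05, one test per outcome, all six null hypotheses true, and week-24 PPA tested alone at 0.05.

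- Five-outcome BH family: with all nulls true and independent tests, the chance of any rejection equals q = 0.05.
- Five-outcome family plus one separate test at 0.05: 1 − (1 − 0.05)(1 − 0.05) = 1 − 0.95² = 0.0975. Simulation with 400,000 replicates gave 0.0976.
- All six in one BH family: 0.05. Simulation gave 0.0500.
- For scale, six wholly unadjusted independent tests: 1 − 0.95⁶ = 0.265.
- With pairwise correlation 0.5 between the six test statistics, simulation gives about 8.4 to 8.5% as listed, against about 4.4 to 4.5% with all six in one family.

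**Step 3. Price of including it.** The BH thresholds are i × q/m.

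- m = 5: 0.010, 0.020, 0.030, 0.040, 0.050.
- m = 6: 0.0083, 0.0167, 0.025, 0.0333, 0.0417, 0.050.

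The smallest step moves from 0.010 to 0.0083.

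**The case against.** The best defence is that week-24 PPA is meant as a later time point of a co-primary endpoint and not as a separate member of the secondary family. Section 2.6.2 does call it a secondary time point. The abstract and the Figure 1 caption name the same five efficacy secondary outcomes as the FDR sentence. That sentence comes straight after the paragraph on secondary continuous outcomes. An exchangeable GEE also makes sense only with repeated abstinence measurements, and weeks 6 and 24 are the only two. This may explain how the list came to have five members. It does not settle the matter, because Section 2.6.1 calls week-24 PPA a secondary outcome outright, the co-primary rule is confined to week 6, and the FDR sentence refers to the secondary outcomes without limiting itself to continuous ones.

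A second defence is that an analysis plan not shown here may place the outcome. It may. But the article is not silent on the family: it enumerates it, and the enumeration conflicts with its own outcome list. The published sentence would need correcting in either case.

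Three objections limit the point, and they stand:

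- A reader might infer that week-24 PPA will be tested at an unadjusted 0.05. The article does not say so. Its 0.05 statements concern the sample size and the co-primaries, and no threshold or success claim is given for week-24 PPA.
- A reader might take 9.75% as this trial's error rate. The article names neither BH nor a q level and fixes no single contrast per outcome. FDR control also targets the expected proportion of false discoveries, which coincides with the chance of any false claim only when all nulls are true.
- A reader might think the trial's conclusion is at risk. It is not, because the success rule uses only VAS change and week-6 PPA. The article also promises cautious interpretation of the secondary findings.

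**Conclusion.** The point holds as an internal contradiction. Six secondary outcomes are declared, control is claimed across the secondary outcomes, and the list behind that claim has five. Week-24 PPA belongs to no stated multiplicity family. The comparison of the two sections needs no assumption.

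The size does rest on assumptions. Under those in the working, the chance of at least one false secondary claim roughly doubles, from 5.0% to about 9.75%, and somewhat less in absolute terms if the outcomes are correlated. This is the effect of one extra test at 0.05. The 5.0% comparator also needs one fixed contrast per outcome, which correcting the list would not by itself provide. The correction should be made before unblinding, but it is not a threat to the primary analysis.

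**What to change.** Add week-24 PPA to the bracketed list in Section 2.10.1, so that the FDR family matches the six outcomes in Section 2.6.2. This takes one line. The cost is slightly stricter thresholds for the other five outcomes, as shown in the working.

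If the sponsor prefers to keep week-24 PPA outside the family, that is also defensible if it is stated: say that it will be reported as an odds ratio with confidence interval and without a confirmatory claim, and reword the control claim so that it refers to the five listed outcomes only. Either choice should be recorded before group allocation is unblinded.

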#### Inclusion criteria

2.2.2

Participants meeting all of the following criteria will be eligible for inclusion:

(1) Aged 18–60 years;(2) Diagnosis of TUD according to the DSM-5 (18);(3) Smoking at least 10 cigarettes per day for at least 1 year;(4) Willingness to quit smoking and to initiate and adhere to nicotine replacement therapy as specified in the study protocol;(5) No acupuncture treatment within the previous 3 months;(6) Ability to provide written informed consent and comply with study procedures.

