### Limitations

3.1

This study has several limitations. First, the single-center design and relatively strict inclusion and exclusion criteria, including the exclusion of individuals with severe psychiatric comorbidities, may limit the generalizability of the findings to broader populations of smokers with tobacco use disorder.

Second, the absence of a sham acupuncture or attention-matched control limits the ability to distinguish specific effects of harmonizing mind acupuncture (HMA) from nonspecific or placebo-related effects, particularly for subjective outcomes such as visual analog scale (VAS) craving, BDI-II, and BAI scores. However, this design reflects the pragmatic objective of the trial to evaluate effectiveness in real-world clinical settings, and comparison with standard care (NRT alone) remains appropriate for informing clinical decision-making. To partially address this concern, biochemically verified 7-day point prevalence abstinence (PPA) has been included as a co-primary outcome, providing an objective measure of cessation that is less susceptible to expectancy effects. Differences in treatment exposure between groups may introduce attention-related bias, although baseline and post-randomization treatment expectancy scores will be collected and incorporated into sensitivity analyses to mitigate this effect.

Third, the 24-week follow-up period may be insufficient to fully capture long-term relapse patterns; future studies should consider extended follow-up durations of at least 52 weeks to better assess sustained abstinence and relapse risk.

Fourth, the technical complexity of the HMA protocol and the requirement to elicit De Qi sensations may introduce inter-practitioner variability despite standardized training and detailed procedural manuals.

Fifth, although missing smoking-status data will be handled as non-abstinent in the primary analysis, sensitivity analyses using MNAR assumptions may still be biased if dropout is related to unmeasured factors such as relapse or adverse events.

Sixth, while the sample size of 220 provides adequate power for both co-primary outcomes (VAS craving change and biochemically verified PPA), the single-center design and relatively strict inclusion criteria may still limit generalizability. Future multicenter studies with more diverse populations are warranted to confirm the findings.

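### The exploratory test of effect modification by age uses only an unexplained split at 40; if the effect changes smoothly with age, this loses a quarter or more of the information

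*Protocol article*

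**What the plan says.** All of this is in the protocol article.

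- **Age range.** Section 2.2.2 (Inclusion criteria) admits participants "Aged 18–60 years". No mean, SD or expected share aged 40 or over is given.
- **Subgroup rule.** Section 2.10.1 plans three-way terms (subgroup, treatment and time) "within mixed-effects models to explore potential effect modification by sex (male/female) and age (<40 vs. ≥40 years". No reason for the cut at 40 is given, and no analysis with age as a continuous variable is described.
- **Models for the co-primaries.** In the same section, craving on the VAS "will be analyzed using linear mixed-effects models including fixed effects for group, time, and group × time interaction", whereas abstinence (PPA) at week 6 "will be analyzed using generalized estimating equations (GEE) with a logit link function and an exchangeable correlation structure". No interaction term is described for the GEE model.
- **PPA visits.** Table 1 and section 2.4.3 schedule PPA at weeks 6 and 24 only.

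**The concern.** Splitting age at 40 treats participants aged 18 and 39 as alike and those aged 39 and 41 as different. If the benefit of acupuncture changes gradually with age, the two-class comparison discards the variation within each class. Interaction tests usually have low power, and the article claims none for these, so information lost here is hard to spare. A null result from the split could be read as no age effect when the test had little chance of showing one.

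A smaller point goes with it. The subgroup terms are placed in mixed-effects models, while PPA is assigned to GEE. It is therefore unclear which subgroup term, if any, applies to the abstinence co-primary.

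**Working it through.** **The plan's own figure.** There is none to reproduce. The article gives no power or sample size for any subgroup analysis.

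**Measure of loss.** Suppose the treatment effect varies linearly with age. Testing the indicator for age ≥40 instead of age itself keeps a share r² of the information, where r is the correlation between age and the indicator. The loss is 1 − r², and the sample size for equal power rises by 1/r².

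**Uniform ages on 18–60 (assumed).** The share below 40 is p = (40 − 18)/(60 − 18) = 22/42 = 0.524. Then r² = 3p(1 − p) = 3 × 0.524 × 0.476 = 0.748. The loss is 25% and the sample-size factor is 1/0.748 = 1.34.

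**Normal ages split at the median (assumed).** r² = φ(0)²/(0.5 × 0.5) = 0.3989²/0.25 = 0.637, a loss of 36%.

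**Normal ages truncated to 18–60 (assumed).** Simulated for means 30 to 50 and SDs 8 to 12, where mean and SD are those before truncation. Losses ran from 31% to 58%.

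**Effect on power.** Take an interaction that continuous age detects with 80% power at two-sided 0.05. With the split, power is Φ[(1.960 + 0.842) × √r² − 1.960].

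| Assumed ages | Share ≥40 | r² | Loss | Power with split |
|---|---|---|---|---|
| Uniform 18–60 | 48% | 0.748 | 25% | 68% |
| Truncated normal 40, SD 12 | 49% | 0.688 | 31% | 64% |
| Truncated normal 40, SD 8 | 50% | 0.652 | 35% | 62% |
| Truncated normal 35, SD 8 | 27% | 0.580 | 42% | 57% |
| Truncated normal 48, SD 8 | 83% | 0.510 | 49% | 52% |
| Truncated normal 50, SD 8 | 88% | 0.443 | 56% | 46% |
| Truncated normal 30, SD 8 | 11% | 0.418 | 58% | 44% |

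At a loss of exactly 50% the power is 51%. The loss exceeds a half only when the split is lopsided.

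**The reverse case.** The measure is symmetric. If the true modification is a step at 40, a linear age term keeps the same r², so it loses the same 25% to 58%. Neither form is best under every truth.

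**Power of an interaction for PPA.** Planning inputs from section 2.3 are control abstinence 15% and OR 1.9. The odds are 0.15/0.85 × 1.9 = 0.335, so the rate with acupuncture is 0.335/1.335 = 25.1%. Assume an even age split of the 220 participants, 55 per arm and age class. Expected quitters per age class are 55 × 0.15 ≈ 8 in control and 55 × 0.251 ≈ 14 with acupuncture. The standard error of the log ratio of ORs is √{2 × [1/(55 × 0.15 × 0.85) + 1/(55 × 0.251 × 0.749)]} = 0.692. The ratio of ORs detectable with 80% power is exp(2.802 × 0.692) ≈ 6.9.

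**The case against.** **The cut is fixed in advance and the analysis is exploratory.** This is fair. A prespecified cut prevents a data-driven one, 40 lies one year from the midpoint (39) of the eligible range, and no success rule depends on the result. An article may also leave out the reason for an exploratory cut. These points limit the weight of the concern. They do not supply the information lost when the split is the only age test.

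**Continuous age is better only if the trend is roughly linear or smooth.** This stands. The documents do not establish the shape, and under a true step at 40 the linear term loses just as much. It is the reason to keep the split results beside the continuous test.

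**A reader might infer that abstinence is excluded from effect-modification analysis altogether.** The documents do not support that. The subgroup sentence says what the analyses will include, not that the list is complete. It omits the word linear, so a logistic mixed model is not ruled out. The article also refers to a statistical analysis plan, which is not shown and may hold the detail. What can be said is that the article specifies no subgroup model for PPA. Even with a logistic mixed model some ambiguity remains: PPA has no baseline value, so the three-way term alone would compare subgroup differences between weeks 6 and 24, not test whether the week-6 effect differs by subgroup.

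**A reader might also infer that no objective smoking outcome is covered.** That does not hold either. Exhaled CO is analysed by mixed models, so the subgroup rule reaches it.

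**Conclusion.** The point holds at low severity. The only age test described is a two-class split at 40, with no reason given, although age is available as a continuous variable. If modification is roughly linear in age, the loss is about 25% for uniform ages and about 31–58% for the truncated normals tried. Power that would be 80% on continuous age then falls to about 68% at a 25% loss, 51% at a 50% loss and 44% in the most lopsided case. These figures rest on assumed age distributions and on linearity; neither is in the article, so they should be read as a conditional range. The 80% starting point is a reference, since the plan claims no power for any interaction.

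The PPA part is a clarification and does not carry the point. With a detectable ratio of ORs near 6.9, an abstinence interaction could give only a wide interval. The primary conclusion is unaffected.

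**What to change.** In section 2.10.1, and in the analysis plan before unblinding:

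1. Make the exploratory age interaction use age as a continuous centred covariate, linear or as a low-order spline, and name the week-6 contrast as the quantity tested.
2. Keep the prespecified <40/≥40 estimates as a supportive display.
3. Optionally, add treatment × age and treatment × sex terms for the week-6 PPA model. Report them as exploratory ORs with 95% CIs, and state that their power is very low.

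This changes wording only and needs no new data or participants. The cost is reliance on an assumed shape: a linear term would lose a comparable share of information if the truth were a step at 40, which item 2 is there to show. A spline relaxes that assumption but spends extra degrees of freedom.
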